### Primary outcome: Welsh Health Survey data

Data on consumption will be used from the five annual consecutive Welsh Health Surveys 2005–09 [41]. Participants were asked to state the highest number of units they had drunk on any one day in the previous seven days, using a standard prompt to convert different types and quantities of alcoholic drinks into units (2005–07) or by reporting measures of consumption translated into units by the dataset coders (2008–09). The classification of units into ordinal categories of consumption used in the Welsh Health Survey dataset is based on the Department of Health definitions (Table 1) [42].

**Table 1 T1:** Categorisation of alcohol consumption in the Welsh Health Surveys 2005-09

**Category**	**Maximum units drunk on any day in the last week**
None	Did not drink in the last seven days
Sensible	Men drinking no more than 4 units, women no more than 3 units
Above guidelines, less than binge	Men drinking more than 4 and up to and including 8 units, women more than 3 and up to and including 6 units
Binge	Men drinking more than 8 units, women more than 6 units

Source: References [42].

### Secondary outcomes

#### Hospital admissions

The SAIL databank includes the complete PEDW database, which records all inpatient and day case admissions for residents of Wales. The pseudonymisation process results in the encryption of a unique, unidentifiable ID that enables a patient-based analysis rather than an admissions-based analysis to be carried out. Each hospital spell has an attached ICD-10 diagnosis code in one of 14 positions: primary, subsidiary, and 3^rd^ to 14th position. The Office for National Statistics has published a list of ICD-10 codes to define causes of death which are exclusively alcohol-related i.e. not just where alcohol could be a contributory aetiological factor [51]. There are several other published classifications of ‘exclusively’ alcohol-related conditions with considerable overlap between them [52]. The differences from the ONS definition largely relate to non-fatal conditions excluded from the ONS cause of death list. In addition are the external causes of morbidity and mortality codes for motor vehicle crashes and injuries resulting from inter-personal violence. However these codes are not alcohol-specific. In the analysis we will define alcohol-related as the combined causes of death and condition codes and we will perform secondary analyses including ICD-10 ‘External’ codes for the motor vehicle crashes and injuries resulting from inter-personal violence.

Each PEDW record is linked to the LSOA of residence to which a deprivation score, such as a quintile, of the Welsh Index of Multiple Deprivation 2005 [53], has been attached in SAIL. We can then attribute admissions to an LSOA and deprivation quintile for the analysis.

### Accident & emergency department data

The Accident & Emergency Department Data Set (EDDS) is a new dataset within HIRU/SAIL and the first wave of data for the 13 Accident & Emergency (A&E) Departments in Wales for 2009 has been cleaned and validated. Data for subsequent years are entered into SAIL as it is received, currently on a monthly basis. Attendances are recorded for all injuries with the date and time of day. There is no definitive uniformly applied code for alcohol-related attendances in this dataset and so we will use attendance at night (midnight to 6am) as a proxy for alcohol-related as the majority of injury attendances at night (particularly aged 16–39) are likely to be alcohol related. These attendances will be linked to RALFs and hence to anonymised network measures for the analysis. Using ALFs/RALFs we will also trace attendees who are subsequently admitted to hospital (by linking to PEDW) and exclude all those who do not have an alcohol-related ICD-10 code.

The numbers are sufficient for a spatial analysis: there were 101 908 night time attendances at the 13 A&E departments in Wales in the financial year 2009/10. The highest numbers were on Friday to Saturday and Saturday to Sunday nights (15 862, 17 098) compared to weekdays (weekday range 13 374 to 14 232; weekly mean 14 558, standard deviation 1386).

### Police data

Police forces record electronically all incidents reported to them. Incidents of violence against the person are detailed according to incident type (e.g. assault occasioning actual bodily harm), the injury incurred, incident location and alcohol use. These incidents are recorded at the premises, address or street location level. Eastings and Northings locations are recorded, facilitating georeferencing into LSOAs, although the accuracy of these coordinates has not been evaluated. Data sharing agreements between Cardiff University and the four police forces in Wales are now in place. Our work with police data on an exploratory trial of a disorder reduction intervention found the data to be sufficiently robust for research purposes [54]. Although a proportion of violent incidents are not reported to the police, these data remain the most detailed and accurate records of violent incidents at the premises or street level.

We conducted pilot work using South Wales Police data to establish the feasibility of using police recorded incident data for the period of the proposed study, 2005–09. Approximately 42% of incidents were recorded as involving alcohol on the part of the offender or the victim. While this rate is slightly below the 50% prevalence among incidents recorded by the British Crime Survey [55] we believe that these data are of sufficient quality for our study. Furthermore, the recording of incident type and presence of injury allows the study to explore the role of outlet density for both occurrence and severity. The Police data aggregated at LSOA-level will be added to SAIL for this study.

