### Estimation of outlet density

Our literature review found four main approaches to estimate outlet density: (1) number of outlets per capita in an administrative unit or geographical area, (2) number of outlets per network miles per geographical area, (3) number of outlets per geographical area defined by walking or drive time (a ‘buffer zone’), and (4) closest Euclidian distance from each subject’s home to an outlet.

We wish to estimate a new measure of outlet density which includes a more realistic and robust measure of accessibility than previously published methods. We will estimate a summary statistic for distance to all outlets from each residence within a defined buffer zone. The measures of distance calculated will be network distances and travel times which will more accurately measure exposure in comparison to Euclidian distances.

We therefore propose a spatial methodology to estimate outlet density using the unique advantages of the WDS population data within the SAIL databank:

(1) We will calculate the sum (or mean) network distance for each individual to each outlet within a meaningful network range (10 minutes walk and 10 minutes drive-time) of each residence (RALF), using the service area tool in ArcGIS Network Analyst module, together with Ordnance Survey MasterMap data and point location facility data in the eGIS [49,50]. The individual-level measure of outlet density exposure will be a function (e.g. reciprocal) of the total (mean) distance;

(2) We will derive the LSOA density by averaging the values for all individual residents in the LSOA.

The primary analysis will be for all alcohol outlets but we will also estimate outlet densities for on and off-sales separately for those authorities who can supply this categorisation.

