### Statistical analysis

The primary analysis will be for all alcohol outlets but we will also analyse the data using outlet densities for on- and off-sales separately where available. Our analysis plan has to take into account the nature of the data available through SAIL. Data on individuals nested within households nested within anonymised LSOAs will be available. Our analysis plan is:

(1) Full descriptive statistics.

(2) Spatial models to explore the relationship between counts/rates of the four outcome measures and outlet density. The models will account for the year and will adjust for aggregated population characteristics, such as the percentages of males and of certain socio-economic groups, and the median age. There are a number of methodologies that could be adapted to calculate spatial autocorrelation, including the Bayesian approach of Besag, York and Mollié [56], the random effects models developed by Gruenewald and colleagues and used in the three Californian longitudinal studies [25,26,34] and geographically weighted regression (GWR) models [57-60]. Moreover, more complex methodologies which take into account network distances – the distance to an outlet based on road and footpath measurements – can be adapted to explore these relationships. These methodologies include network distance calculations [61], the two-step floating catchment technique [62-64], and modified GWR models [65]. The different types of spatial models make different assumptions, model spatial autocorrelation differently and analyse the data in different ways; their relative merits will be explored as part of the study.

(3) A multilevel analysis using the hierarchy outlined above. We will use multilevel ordinal models of the defined categories of consumption for the WHS data and multilevel logistic models of the odds of hospital admission and A&E attendance as a function of change in individual outlet exposure, adjusting for confounding individual variables (age, gender, socio-economic status) and LSOA deprivation quintile. This method cannot be used for the crime data as we only know the location of offence with no information on individuals. Multilevel modelling is a well-established technique, see for example Goldstein 2003 [66], and we will fit models using the standard MLwiN [67] and R software [68].

In order to address the secondary research questions:

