### Research governance and ethical arrangements

The information governance requirements for use of the Secure Anonymised Information Linkage (SAIL) dataset in this study have been approved by the Independent Information Governance Review Panel (IGRP), with membership comprised of senior representatives from the British Medical Association (BMA), the National Research Ethics Service (NRES), Public Health Wales, NHS Wales Informatics Service (NWIS), and Involving People.

Participant consent is not required because all the SAIL study outcome data on patients (hospital admissions and A&E attendances) will be anonymised before they are incorporated into the SAIL databank. As the SAIL databank is fully anonymised, it does not fall into the remit of the National Information Governance Board who provide section 251 (formerly section 60) exemption to use identifiable data without consent.

The anonymised Welsh Health Survey dataset is supplied under a formal Data Access Agreement between Cardiff University and the Welsh Government. Welsh Health Survey data do not have permission from the Data Owner (Welsh Government) to link into SAIL at individual-level but can be linked, using data aggregated by LSOA, to outlet density exposures. Police data are also supplied under Data Access Agreements between each Police Force in Wales and Cardiff University and can also only be linked at aggregate LSOA-level.

The Chairman of the Research Ethics Committee for Wales has confirmed in writing that this study does not require ethical approval under NHS research governance arrangements.

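### Study 4 counts violent crime where it happens, but the only LSOA outlet density defined is averaged over where residents live, so a null crime result would be hard to interpret.

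*Protocol article*

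**What the plan says.** **Outcome.** The Police data section gives the spatial reference of each incident: "These incidents are recorded at the premises, address or street location level". It continues: "Eastings and Northings locations are recorded, facilitating georeferencing into LSOAs", with the caveat that nobody has yet assessed how accurate the coordinates are. The Statistical analysis section rules out a multilevel model for crime "as we only know the location of offence with no information on individuals". The research governance section adds that police data "can also only be linked at aggregate LSOA-level".

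**Exposure.** The section on estimating outlet density starts from the home. It summarises network distance to each outlet "within a meaningful network range (10 minutes walk and 10 minutes drive-time) of each residence (RALF"), and the individual exposure is some function of the total or mean distance, with the reciprocal given as an example. The LSOA value follows: "We will derive the LSOA density by averaging the values for all individual residents in the LSOA".

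**Model.** The Statistical analysis section plans "Spatial models to explore the relationship between counts/rates of the four outcome measures and outlet density", adjusted for aggregated characteristics of the population. It defines no separate density for crime.

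**Residents who move.** The same section says the yearly exposure follows people who change address. It plans to repeat the models with densities recomputed for the baseline population.

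**The concern.** For consumption, hospital admissions and A&E attendance, outcome and exposure both belong to the resident. For crime they do not: the outcome belongs to a place and the exposure to the people who live there. The two can differ most in town-centre LSOAs, where many of the people present at night may live elsewhere.

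The article's own literature review names violence as the harm most often studied in relation to outlet density, and Study 4 is its test using police records. With around 47,000 offences a year, a null result would probably be read as evidence of little effect. It could equally mean that the exposure does not describe availability at the places where offences happen, and the plan offers no second measure to tell the two apart.

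**Working it through.** The document states no power or effect figure for Study 4, so there is none to reproduce. The check is a comparison of definitions, followed by three short derivations.

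**1. What each quantity is indexed by**

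| Quantity | Indexed by | Section |
|---|---|---|
| Crime count | LSOA of the incident | Police data |
| Individual exposure | Home | Estimation of outlet density |
| LSOA density | Mean over homes of residents in the LSOA | Estimation of outlet density |
| Adjustment variables | Population characteristics | Statistical analysis |
| Use of density | All four outcomes | Statistical analysis |

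The crime count and the density share an LSOA label but not a population. The density also draws on outlets outside the LSOA, up to 10 minutes' drive from its homes.

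**2. Movement of residents alone can change the density**

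Suppose an LSOA has two groups of homes with exposure values x1 and x2, and a share p of residents lives in the first. Then

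D = p·x1 + (1 − p)·x2.

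If no outlet opens or closes, x1 and x2 stay fixed. If the share moves to p′, then

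change in D = (p′ − p)(x1 − x2).

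This is not zero unless the shares or the two values are equal. For a resident outcome it is a real change in exposure. For an offence-location outcome it is change in the exposure variable without any change in outlets.

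**3. The sign of the response to a new outlet is not fixed**

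- Reciprocal of the total: the total T becomes T + d, so 1/T falls.
- Reciprocal of the mean: with n outlets at mean distance m, the new mean is (n·m + d)/(n + 1). This exceeds m when d > m, so the reciprocal falls for homes where the new outlet lies beyond their current mean distance, and rises when it is nearer.

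The article leaves the function open, so one cannot say that a new outlet raises the measure in surrounding LSOAs.

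**4. Can the blurring be sized?**

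Inputs from the document: around 47,000 offences a year (Design) and 1,896 LSOAs (Data sources), so 47,000 / 1,896 = 24.8 offences per LSOA per year on average. Neither the number of LSOAs in a buffer nor the spatial pattern of outlet change is given.

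A simulation under assumptions that are not in the document shows how much depends on them. It used a 44 × 44 grid, outlet change averaged with equal weights over cells within a set radius, and a share w of the variance of change being spatially smooth. The correlation between a cell's own change and the averaged change was:

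| Radius (cells) | w = 0 | w = 0.5 | w = 0.8 |
|---|---|---|---|
| 1 | 0.44 | 0.68 | 0.79 |
| 2 | 0.28 | 0.63 | 0.77 |
| 4 | 0.14 | 0.44 | 0.55 |

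A range of 0.14 to 0.79 from assumed inputs supports no single figure for information lost. Correlation is also symmetric: if violence responds to outlets across the whole buffer, the own-cell count is the poorer measure. The size and direction of the bias therefore stay undetermined.

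**The case against.** The case for leaving the plan alone has real content.

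- **The exposure is still tied to the place.** The residents' homes lie in the LSOA where the offences are counted. This stands: the measure is blurred, not unrelated.
- **A common exposure helps comparison across the four studies**, and the research question concerns harm in the community. This supports keeping the resident average in Study 4, but not having it as the only measure.
- **Other spatial methods are listed**, including floating catchment and modified geographically weighted regression, and mapping will inform the specification of the density variable. However, none of these is assigned to crime, and nothing says the crime exposure will be based on outlet location.
- **The baseline-population re-analysis** would show how far movement of residents drives the results. It answers part of the second derivation, but the measure remains home-based.

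Four stronger readings are tempting and are not supported:

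- A reader might infer that a new town-centre outlet raises the density of every LSOA within 10 minutes' drive. Under the reciprocal examples the measure can fall.
- A reader might infer that the crime effect is diluted by a computable fraction. That needs independent outlet changes, equal weights and an effect confined to the offence LSOA. The article states none of these, and its remarks on local licensing policies suggest that changes cluster.
- A reader might infer that crime will be analysed as a rate per resident. The article describes the study population for the outcomes other than consumption as people living in Wales, but the models allow counts or rates and no crime denominator is fixed.
- A reader might infer that everything needed for a place-based measure is already in the eGIS. Its description does not list the licence registers or LSOA boundaries, and the sample size section says outlet locations by year were not yet held.

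**Conclusion.** The concern holds as a mismatch of definitions: an offence-location outcome is related to an exposure that depends on where residents live and can change when they move. The consequence is that a null finding for crime could not be separated from a poorly matched exposure. This rests on the text, and on the assumption that an appreciable share of offenders or victims live outside the LSOA of the offence. The document gives no figure for that share and says that nothing is known about the individuals.

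No numerical size is claimed, and it does not follow that a null result would be an artefact. Study 4 is one of three secondary outcomes, so the point should be dealt with but does not threaten the primary analysis.

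**What to change.** For Study 4, pre-specify an LSOA density based on outlet location: outlets in the LSOA and within the walking network range of it, not averaged over residents. Report it alongside the resident-averaged density, so that agreement or disagreement between the two is visible.

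Model offence counts. If rates are used, state a denominator that does not assume the people at risk are the LSOA's residents.

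This is feasible with the planned data. The Alcohol outlets section says postcodes allow each outlet to be placed within any boundary, and an LSOA-level density is compatible with the LSOA-only linkage of police data.

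The cost is one additional exposure measure for Study 4 that differs from Studies 1 to 3, with some extra GIS and analysis work once the outlet registers from the 22 authorities have been geocoded.

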For the other outcomes the study population is essentially the 2.4 million people living in Wales aged at least 16 years. The outcomes are not rare with approximately 13 000 alcohol-related admissions, 100 000 night time A&E attendances, and 47 000 violence against the person crimes in Wales annually. We will have very high power for detecting small differences between LSOAs at the extremes of changes in alcohol outlet density. For example there would be over 80% power for identifying a reduction from 5.4 per thousand per annum to 5 per 1000 per annum in hospital admissions between the extreme quintiles of change in outlet density. While this ignores clustering within LSOA, that effect is unlikely to be so large that the power is greatly reduced and there will be more power for detecting a larger difference. If the correction factor for clustering was two, a common finding in studies of this type, the required sample size would effectively be doubled. However with the planned sample size there would still be over 80% power for detecting a reduction from 5.4 per thousand per annum to 4.8 per thousand per annum in the admission rate for alcohol-related conditions.

### Statistical analysis

The primary analysis will be for all alcohol outlets but we will also analyse the data using outlet densities for on- and off-sales separately where available. Our analysis plan has to take into account the nature of the data available through SAIL. Data on individuals nested within households nested within anonymised LSOAs will be available. Our analysis plan is:

(1) Full descriptive statistics.

(2) Spatial models to explore the relationship between counts/rates of the four outcome measures and outlet density. The models will account for the year and will adjust for aggregated population characteristics, such as the percentages of males and of certain socio-economic groups, and the median age. There are a number of methodologies that could be adapted to calculate spatial autocorrelation, including the Bayesian approach of Besag, York and Mollié [56], the random effects models developed by Gruenewald and colleagues and used in the three Californian longitudinal studies [25,26,34] and geographically weighted regression (GWR) models [57-60]. Moreover, more complex methodologies which take into account network distances – the distance to an outlet based on road and footpath measurements – can be adapted to explore these relationships. These methodologies include network distance calculations [61], the two-step floating catchment technique [62-64], and modified GWR models [65]. The different types of spatial models make different assumptions, model spatial autocorrelation differently and analyse the data in different ways; their relative merits will be explored as part of the study.

(3) A multilevel analysis using the hierarchy outlined above. We will use multilevel ordinal models of the defined categories of consumption for the WHS data and multilevel logistic models of the odds of hospital admission and A&E attendance as a function of change in individual outlet exposure, adjusting for confounding individual variables (age, gender, socio-economic status) and LSOA deprivation quintile. This method cannot be used for the crime data as we only know the location of offence with no information on individuals. Multilevel modelling is a well-established technique, see for example Goldstein 2003 [66], and we will fit models using the standard MLwiN [67] and R software [68].

In order to address the secondary research questions:

(4) We will assess the impact on health inequalities by firstly stratifying the spatial and multilevel models using quintiles of the Welsh Index of Multiple Deprivation to examine whether the modelled associations vary with deprivation category. This method was used for postcode sectors in the Australian longitudinal analysis [29]. A further method which we will use is to model the interaction between LSOA deprivation score and change in outlet density and the two-way interaction including individual SES (using the NS-SEC) [69]. This method uses the whole dataset and the coefficients of the interaction terms give information on the effect on inequalities over time.

(5) Since the annual estimation of outlet density exposure automatically includes people who move residence, (from using the WDS within SAIL), our main models will correct for population migration. We will assess the impact of population migration by re-estimating annual outlet densities using the baseline population, repeating the models above, and comparing to the main models. Health selection bias can thus be assessed.

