### Primary research question

Overall, there is cross-sectional evidence from mainly American studies to suggest that higher outlet density is associated with alcohol-related harm, particularly involving violence. The evidence from longitudinal studies for associations between harm and a change in outlet density is less well established. Many methodological questions remain over the best way to measure outlet density and how to model the data. Little is known on the effect of a change in outlet density on inequalities in alcohol-related health and the role of population migration. Our primary research question for this study is:

What is the impact of a change in the density of alcohol outlets on alcohol consumption and alcohol-related harms to health in the community?

Our secondary research questions are:

1. Does a health selection effect from population migration at small-area level explain any observed associations between outlet density and alcohol-related harm?

2. What effect does change in outlet density have on population inequalities in alcohol-related health?

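### The individual-level admission and A&E models omit each person's own alcohol-related admission before baseline, which the linked data could supply and which may confound the outlet effect

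*Protocol article*

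**What the plan says.** For hospital admission and A&E attendance, item (3) of the Statistical analysis section plans multilevel logistic regressions on each person's change in exposure. It states the covariates as: "adjusting for confounding individual variables (age, gender, socio-economic status) and LSOA deprivation quintile". Item (2), on the spatial models, offers its covariates only as examples. Item (3) names its four without that qualification. The hierarchy is described as "Data on individuals nested within households nested within anonymised LSOAs will be available", and no level for repeated occasions within a person is stated.

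The Hospital admissions section says: "The SAIL databank includes the complete PEDW database, which records all inpatient and day case admissions for residents of Wales". On what the linkage makes possible, the same section adds: "The pseudonymisation process results in the encryption of a unique, unidentifiable ID that enables a patient-based analysis rather than an admissions-based analysis". The Accident & emergency section also links attenders to the admissions database, but only to follow those admitted afterwards.

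The first secondary research question is: "Does a health selection effect from population migration at small-area level explain any observed associations between outlet density and alcohol-related harm". Item (5) answers it by recalculating outlet densities for the baseline population, refitting the models and comparing them with the main ones. No term, stratum or exclusion based on earlier admissions appears anywhere in the article.

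**The concern.** A past alcohol-related admission plausibly predicts a further one strongly. To confound the outlet effect, it must also be associated with change in exposure. The protocol supplies a route: exposure is measured at the person's own residence each year, so moving house changes it. If people with alcohol-related illness move differently from others, illness before the exposure window affects both exposure change and later admission.

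The four listed covariates do not capture this, because people alike on all four can differ in history. Item (5) addresses the part of exposure change caused by moving. It contains no measure of health, so it cannot show whether movers were already ill, or whether earlier illness differs across exposure change among people who stayed. At stake are the individual-level outlet odds ratios for two secondary outcomes and the answer to the first secondary question.

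**Working it through.** The documents give no figure for this point, so there is none to reproduce. The check asks how large a bias could be, and what the available data could flag.

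**Inputs from the protocol (Proposed sample size)**
- About 13 000 alcohol-related admissions a year among 2.4 million adults: 13 000 / 2 400 000 = 0.0054, or 5.4 per 1000.
- Planned contrast between extreme quintiles, 5.4 to 5.0 per 1000: 1 − 5.0/5.4 = 7.4%.

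**Assumed inputs (not in the documents)**
- q, the share of adults with an earlier alcohol-related admission: 1% to 2%.
- R, their admission rate relative to other adults: 10 to 40.
- r, their share in one extreme quintile of exposure change relative to the other: 1.1 to 1.3. This must be read as the imbalance left after the listed adjustments.

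**Formula, with no true outlet effect**

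Spurious rate ratio = [(1 − qr) + qrR] / [(1 − q) + qR] = [1 + qr(R − 1)] / [1 + q(R − 1)]

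| q | R | r | Calculation | Spurious ratio |
|---|---|---|---|---|
| 1% | 10 | 1.1 | 1.099 / 1.090 | 1.008 |
| 2% | 20 | 1.2 | 1.456 / 1.380 | 1.055 |
| 2% | 40 | 1.3 | 2.014 / 1.780 | 1.131 |
| any | any | 1.0 | numerator = denominator | 1.000 |

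**Share of admissions from people with a history:** qR / (1 − q + qR). At q = 1%, R = 10 this is 0.10/1.09 = 9%. At q = 2%, R = 40 it is 0.80/1.78 = 45%.

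**Imbalance needed to mimic the whole planned contrast:** 0.0741 × [1 + q(R − 1)] / [q(R − 1)].
- q = 2%, R = 40: 0.0741 × 1.78/0.78 = 17% lower share.
- q = 1%, R = 10: 0.0741 × 1.09/0.09 = 90% lower share.
- q = 0.5%, R = 10: 0.0741 × 1.045/0.045 = 172%, which is impossible.

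**What a single run-in year could flag.** One year has about 13 000 admissions, and one person may have several, so at most 0.54% of adults are flagged. That is at most 54% of the history group if q is 1%, and 27% if q is 2%. A group of 0.54% at R = 20 and r = 1.2 carries a spurious ratio of 1.1235/1.1029 = 1.019, against 1.055 for a 2% group.

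**Timing.** Study 2 uses admissions from 2005 to 2009, the same years as the outlet change. The article does not say which earlier years are held. Study 3 uses A&E attendances from 2009 to 2011. Admissions during 2006-09 precede most of those attendances but fall within the outlet-change period, so they may be effects of exposure and are not a clean baseline.

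**The case against.** A reader might infer that people already ill before outlets changed are counted as harm caused by the change. The documents do not support that. If earlier illness is unrelated to exposure change given the four covariates, it raises admission rates at every exposure level and does not produce an outlet effect. This objection stands in full.

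A reader might also infer that, without separating new cases from recurrences, the study cannot say whether outlet change created harm. That does not follow either. The primary question concerns alcohol-related harm in the community, and a readmission brought about by easier access is harm under it. The separation is informative, but its absence is not an error in the aim.

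The route to bias is also limited. For people who stay put, exposure changes because outlets open or close. Personal history is linked to that mainly through the make-up of the area, which deprivation quintile and the area and household levels partly handle. The clearer route is moving house, and item (5) does plan a comparison for it. That narrows the concern but does not remove it, because the comparison uses no health measure.

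Finally, all three bias inputs are assumptions, and the imbalance after adjustment, which matters most, has no support in the documents. That stands, so the range above shows possibility, not likelihood.

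**Conclusion.** The omission is real and worth correcting. The covariate list for the Study 2 and Study 3 individual-level models lacks a pre-baseline value of the outcome, the admissions database is linked at person level, and the planned check on health selection does not substitute for it. Whether the omission biases the outlet odds ratio depends on one condition that the documents cannot settle: an association between earlier illness and exposure change that remains after the listed adjustments.

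The size is unknown. Under the assumptions shown, the spurious ratio lies between 1.01 and 1.13. The low end is negligible, the upper part exceeds the 7.4% planned contrast, and with no remaining imbalance there is no bias. The concern is confined to the individual-level models of two secondary outcomes. The primary consumption outcome and the spatial models in item (2) are outside it.

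**What to change.** - Add one binary term, alcohol-related admission before the start of the exposure window, to the Study 2 and Study 3 individual-level models, at least as a pre-specified sensitivity analysis.
- Report the outlet effect separately for people with and without that history. This gives the first secondary question a direct health measure alongside the comparison in item (5).
- Take the history from admission records before 2005 where they are held, and state which years are used.
- If they are not held, for Study 2 treat 2005 as a run-in and count exposure change and outcomes from 2006. State that one year captures only part of the history, at most about 0.5% of adults.
- For Study 3, use only history dated before the exposure window begins. Do not adjust for admissions during 2006-09. The 2005 run-in with 2006-09 outcome years does not carry over to this study, whose outcomes run from 2009 to 2011.

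The cost is one derived variable from data already linked, one extra split of the results, and a stated rule for people whose earlier history is incomplete because they moved into Wales. If the run-in is needed, Study 2 loses one of its five outcome years.
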